# INTRODUCTION

Periodontal diseases are a group of clinical diseases that affect the periodontal tissues of tooth, the two important clinical groups are gingivitis and periodontitis. Gingivitis is a localized inflammation of the marginal periodontium, however periodontitis is an inflammatory process that extends to the supporting tissues of the tooth and is characterized by apical migration of the junctional epithelium, the progressive destruction of the periodontal ligament and alveolar bone.

The importance of the study and treatment of this disease it is due to the high prevalence and clinical consequences; The continuous loss of periodontal support ends with tooth loss, but the effects of this pathology are not only limited to the odonto-stomatological field.

In the last decades, there have been great advances in the field of the etiopathogenesis of periodontal disease, being a complex entity where several factors intervene such as microbiology, hygienic habits, genetics or systemic modifying factors.

Basic research in periodontics follows a path in line with the advances that occur in other fields of science such as medicine, biology, biochemistry ... etc, so that in the periodontal discipline has passed in a few years of studies based in anatomopathology to today, where the study of pathology is increasingly addressed at the genetic and molecular level.

The main differentiating characteristic of periodontitis with respect to the rest of periodontal pathologies is the loss of periodontal support which explicitly involves the resorption of alveolar bone. Consequently, one of the main objectives of the treatment is to prevent the bone loss from.

Regarding the mechanism of bone resorption that occurs in periodontitis, it is known that several factors associated with the host immune response are implicated, as well as innumerable paracrine signals capable of stimulating or inhibiting bone loss.

But, undoubtedly, a great step in the knowledge of bone metabolism was the discovery, at the end of the 90s, of the RANK / RANKL / OPG axis, this being the cornerstone of the osteoclastogenesis process and, therefore, the regulator of bone resorption.

The RANKL (Activator Receptor for Nuclear Factor κ B Ligand **)** is a protein that stimulates the differentiation of osteoclasts that exerts its action by binding to the transmembrane receptor RANK (Activator Receptor for Nuclear Factor κ B), present in preosteoclasts, instead OPG (osteoprotegerin) acts as a decoy ligand binding to RANKL and inhibiting its osteoclastogenic action.

This discovery has been a great advance in the field of medicine, with applications in multiple diseases that occur with alterations in bone metabolism, including the oncological field.

In the specific field of periodontics, the first investigations arose at the beginning of the year 2000, the results of these studies have demonstrated the existence of high RANKL values and low levels of OPG locally in the affected sites of periodontitis.

Of all the methods used for the determination of these molecules, the studies with greater future clinical application are those that value the concentration of these molecules at the level of the crevicular fluid because it is a non-invasive technique.

At present, there are few publications that determine these mediators at the level of the crevicular fluid, in addition different methodologies have been used, which makes it difficult to obtain conclusions of clinical application. Although these publications have contributed important knowledge to better understand the mechanisms of regulation of bone remodeling of the periodontium, we have not found any study that assesses the impact of periodontal therapy on these markers. Therefore, the intention of this research work is to develop a clinical protocol for the taking of samples and determination of RANKL and OPG at the level of the crevicular fluid in patients with periodontitis, and later to determine the changes that occur in their concentrations when performs basic periodontal therapy.

Studies in this direction can provide new information of clinical interest that allows the use of RANKL and OPG as possible markers of the destructive activity of periodontitis, which would allow it to be used in diagnosis, prognosis and in the control of periodontal treatment.

# HYPOTHESIS

The importance of RANKL, RANK and OPG in the regulation of osteoclastogenesis is clear, which has allowed a better understanding of bone metabolism in both physiological and pathological conditions.

The study of possible determinants of periodontal destructive activity has been one of the major topics of interest in the field of periodontics. There are many studies that relate the levels of certain cytokines and other molecular mediators to destructive activity, but undoubtedly the discovery of the RANKL / RANK / OPG axis has allowed us to understand how the actions of various molecules involved in bone remodeling are integrated, because it is the final step that determines ostoclastic differentiation and activation.

The investigations published so far seem to indicate that RANKL concentrations are elevated in the periodontal tissues as well as in the crevicular fluid of patients with periodontitis. However, we have little information about whether the RANKL concentration can be related to the degree of severity of the pathology or to the phases of activity, or if there could be a different profile in the clinical forms of periodontitis, aggressive or chronic.

Regarding OPG concentrations, it seems clear that OPG levels are higher in periodontally healthy individuals or who only suffer from gingivitis. In patients with periodontitis, OPG levels are lower or even markedly lower in cases of aggressive periodontitis.

In view of the results of the investigations published up to now, it can be concluded that the RANKL / OPG ratio is higher in periodontitis than in gingivitis or in health situation. According to current knowledge, the cells responsible for RANKL expression at the periodontium level are fibroblasts (gingival and periodontal ligament), osteoclasts and osteoblasts; but in the presence of periodontitis, the main ones responsible for the expression of RANKL seem to be activated T and B lingotites. This fact would explain how the defensive system of the host against microorganisms of the bacterial biofilm would be the mediating mechanism of osteoclastogenesis (Osteoimmunology).

Despite the documented involvement of RANKL and OPG in periodontal disease, there are still several questions regarding the behavior of these mediators in the etiopathogenesis of this pathology, as well as the clinical utility they may have as markers of periodontal disease.

With respect to this last question, the response that occurs in these molecular mediators when performing basic periodontal therapy has not been studied.

Our main work hypothesis contemplates that basic periodontal treatment (scaling and root planing plus oral hygiene instructions) has an effect on the concentration of RANKL and OPG in the crevicular fluid of patients with periodontal disease, and there is a decrease in the RANKL ratio. OPG, reducing the absolute values of RANKL and increasing those of OPG.

# OBJECTIVES

The general objective of this research is to study the impact of basic periodontal treatment on the ratio of RANKL / OPG in the crevicular fluid of patients with periodontitis.

The main objectives are:

1º In the group of patients with periodontal disease we intend to study if the degree of periodontal health is related to the concentration of RANKL and OPG in the crevicular fluid. For this, we propose these specific objectives:

- 1. Assess the differences between healthy locations, with gingivitis and with periodontitis.
  2. Determine the differences in the levels of RANKL and OPG between locations with and without inflammation (bleeding on probing).
  3. To evaluate if the degree of severity of periodontitis (initial, moderate or advanced) is related to the levels of RANKL and OPG.
  4. To study the behavior of the levels of these molecular mediators after the basic periodontal treatment.

2º The second main objective is to study the differences in the levels of RANKL and OPG in the crevicular fluid between a group of periodontally healthy individuals and another group of patients with periodontal disease. For this we propose three specific objectives:

- 1. To compare the average levels of RANKL and OPG obtained in healthy individuals with those obtained in periodontal patients.
  2. To compare the levels of RANKL and OPG in healthy locations of healthy individuals with the levels obtained in healthy locations of periodontal patients.
  3. Contrast the levels of these molecular mediators obtained in periodontally healthy individuals with periodontal patients who have been treated with basic periodontal treatment.

# 5. MATERIAL Y METHOD

## SAMPLE

Sample of 30 subjets will be studied, which will be obtained from the staff of the Faculty and from the patients who come to first visits in the Periodontics Unit of the Odontology Clinic of the University of Valencia.

The 30 individuals will be divided into two study groups:

**Control sample** : 15 periodontally healthy individuals

**Study sample** : 15 patients with periodontal disease.

Inclusion criteria:

To be included in the study, individuals must read and sign the consent document, and they must commit to faithfully comply with the study protocol.

## 1.- Control sample:

Healthy individuals will be considered those who, both clinically and radiographically, do not present signs or symptoms of periodontal disease in any of their teeth.

## 2.- Sample study:

To be included in the sample, each patient must have been diagnosed with chronic periodontitis, and also have at least one uniradicular tooth for each of the following clinical situations:

- *Healthy tooth* : probing depths less than or equal to 3 mm, without recession and without bleeding on probing.
- *Tooth with gingivitis* : probing depths equal to or less than 3 mm, without recession and with bleeding on probing.
- *Teeth with moderate periodontitis* : Insertion loss greater than 3 mm. and less than 6 mm.
- *Tooth with severe periodontisis* : Insertion loss greater than 6 mm.

Exclusion criteria:

1.- Patients with aggressive periodontitis.

2.-Presence of systemic alterations or taking drugs that alter bone metabolism (osteoporosis, arthritis, hormonal treatment, bisphosphonates, anti-inflammatory drugs, immunosuppressants ... etc).

3.-Having received antibiotic, anti-inflammatory, contraceptive treatment in the last three months. 4.- Primary or secondary occlusal trauma in any of the teeth included in the studies.

5.- Have received periodontal treatment in the last 3 months. 6.- Be in orthodontic treatment.

Exclusion criteria during the study:

1.- Taking any drug that may alter the response to periodontal treatment (anti-inflammatories, antibiotics, antiseptic mouthwashes).

2.- Any drug that can alter bone metabolism.

In the same way, the impossibility on the part of the individual of strict compliance with the rules of the protocol will be an exclusion criterion.

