## CLINICAL PARAMETERS:

- **Clinical history data:**

Patient's age Systemic pathologies Medication

Smoking habit

Hygienic habits (material, frequency, technique and time)

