## SAMPLING OF CREVICULAR AND PROCESSED FLUID:

On the same day of the clinical examination, 4 samples of crevicular fluid were collected from each of the uniradicular teeth with the 4 clinical situations described in the inclusion criteria.

Remove the supragingival plaque with a sterile curette without touching the gum, wash with plenty of water, insulate with cotton rollers and air dry to avoid contamination with saliva.

Insert the Perio Paper® tip until resistance is felt and leave it for 30 seconds. NOTE: If the paper is stained with blood or debris, the sample is contaminated and must be retaken.

Measure the volume of each sample using the Periotron 8000® and the appropriate software.

Place the paper tips in a sterilized Eppendorf tube, add 100 microliters of buffer (PBS together with protease inhibitors) to the sample and centrifuge at 15,000 for 5 min.

Add another 100 microliters of buffer and centrifuge again at 15,000 for 5 min.

Store 200 microliters of each sample at -80ºC until the ELISA test.

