## INTERVENTION IN THE SAMPLE CASES:

In the group of patients belonging to the sample cases, after having collected all clinical and radiological data and samples of crevicular fluid, basic periodontal treatment will be carried out. The treatment consists of scaling and root planing of the 4 quadrants without the use of antiseptics or local action antibiotics. As part of the treatment, patients will be instructed in oral hygiene, both in brushing techniques and in the use of interproximal hygiene measures. At 4 weeks they will be scheduled to re- evaluate clinically and take samples of the crevicular fluid again.

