## SEQUENCE OF THE PROTOCOL:

Day 0 .- Confirmation of adequacy to the inclusion and exclusion criteria of the study. The patient will be explained what the study consists of, the protocol to be followed and the patient's consent. Realization of anamnesis, and collection of clinical and radiological data.

Day 7.- Samples of crevicular fluid will be taken from the selected areas and the samples will be processed.

Day 14.- Periodontal treatment (group of cases): 2-quadrant scaling and root planing and instructions on oral hygiene.

Day 21 .- Periodontal treatment (group cases): Scraping and root planing of the 2 remaining quadrants and oral hygiene instructions.

Day 49.- Group cases: Periodontal revaluation, clinical records and sampling of crevicular fluid. Processing of the samples

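### Antiseptic mouthwash is barred during the study but has no look-back at entry, so the before-after change may mix stopping a rinse with the effect of treatment

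*Protocol*

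**What the plan says.** All the relevant eligibility rules stand in the Protocol under 2.- Sample study.

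- Entry criterion 3 excludes "Having received antibiotic, anti-inflammatory, contraceptive treatment in the last three months".
- Entry criterion 5 excludes those who "Have received periodontal treatment in the last 3 months".
- The first exclusion during the study is "Taking any drug that may alter the response to periodontal treatment (anti-inflammatories, antibiotics, antiseptic mouthwashes".

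Three other places bear on whether mouthwash use before entry is controlled.

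- The Hypothesis section describes basic periodontal treatment as "scaling and root planing plus oral hygiene instructions".
- Intervention in the Sample Cases says that the treatment is given "without the use of antiseptics or local action antibiotics".
- Clinical Parameters lists "Hygienic habits (material, frequency, technique and time" among the history items, together with medication.

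On timing, Sequence of the Protocol puts eligibility, consent, history and clinical data on Day 0. For Day 7 it says "Samples of crevicular fluid will be taken from the selected areas and the samples will be processed". Treatment follows on Days 14 and 21, and the cases are sampled again on Day 49. The section on sampling of crevicular fluid says instead "On the same day of the clinical examination, 4 samples of crevicular fluid were collected".

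**The concern.** The Protocol itself puts three classes of agent together as able to change the response to treatment: anti-inflammatories, antibiotics and antiseptic mouthwashes. Two of them have a three-month look-back at entry. The third has none. The during-study rule then forces any current user to stop, so the Protocol creates a change in exposure between the two samples of that patient.

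Specific objective 4 of the first main objective is a within-patient comparison before and after treatment in 15 patients. The controls are periodontally healthy, untreated, and have no second sample in the schedule. No group shows what happens to RANKL and OPG in a periodontitis patient who stops rinsing and is not treated. If stopping shifts these markers, the shift is counted as part of the treatment effect.

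**Working it through.** The Protocol states no figure on this point, so the check compares the lists and counts days.

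**1. The two lists, agent by agent**

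| Agent | Look-back at entry | Barred during the study |
|---|---|---|
| Antibiotics | 3 months | yes |
| Anti-inflammatories | 3 months | yes |
| Antiseptic mouthwashes | none | yes |
| Contraceptives | 3 months | not named |

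**2. Does another rule close the gap?** Criterion 5 covers earlier periodontal treatment. Given how the Hypothesis section describes basic treatment, ordinary home rinsing does not clearly fall under it. The history items are recorded but are not an eligibility rule. The ban on antiseptics in the intervention section concerns what is given as treatment, not what the patient used before. The gap stays open.

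**3. Days since stopping.** Assume that a regular user stops on Day 0, the day of consent.

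- Baseline fluid under the visit schedule: 7 - 0 = 7 days.
- Baseline fluid if taken on the day of the clinical examination, which the schedule puts on Day 0: 0 days.
- Follow-up fluid: 49 - 0 = 49 days. Check on the schedule: 49 - 21 = 28 days, the four weeks stated in the intervention section.
- Look-back for the other two classes: three months, about 90 days.

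The time off the rinse is therefore 0 to 7 days at the first sample and about 49 days at the second.

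**4. Effect on the mean change.** Let k of the 15 patients be regular users, and let w be the shift in a user's measured change that is due to stopping. Neither k nor w is in the documents. The mean change is displaced by k*w/15:

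- k = 1: 1/15 = 0.07w
- k = 3: 3/15 = 0.20w
- k = 5: 5/15 = 0.33w

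If w is zero, so is the displacement. If the rinse acts in the same direction as treatment and part of its effect remains at baseline, stopping works against the treatment effect and the measured change is too small. That direction is also an assumption.

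**The case against.** The two lists may serve different purposes: past exposure at entry, concurrent use during the study. They differ in the other direction too, since contraceptives appear only at entry. A window meant for systemic drugs need not suit a rinse, and criterion 5 could cover a rinse prescribed as therapy. Hygiene habits and medication are recorded, so users can probably be identified and a sensitivity analysis run. The statistical analysis plan is not at hand and may provide one. All of this is fair and lowers the weight of the point. It does not close the gap for self-use, and setting users aside afterwards would cost patients from a group of only 15.

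Four stronger readings are tempting, and the documents do not support them.

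- *That the baseline is known to carry a rinse effect.* The Protocol says only that such agents may alter the response to treatment. It gives no duration of effect and no effect on RANKL or OPG before treatment.
- *That the loss can be stated as a percentage.* If a share p of patients are users and the rinse has already given a share s of the treatment change, the measured change is 1 - p*s of the true one. Taking p = 0.2 and s = 0.25 gives 95%, and p = 0.4 and s = 0.5 gives 80%. Nothing in the documents anchors p or s, and the formula allows no fading over the 7 days before sampling.
- *That teeth are wrongly graded healthy.* The Protocol defines a healthy tooth by its observed state, including absence of bleeding. If fluid is taken on the examination day, grade and fluid reflect the same exposure. A mismatch can arise only if sampling is on Day 7.
- *That three months is the right window for a rinse.* The documents justify no window for mouthwash.

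**Conclusion.** The entry and during-study exclusions are inconsistent for antiseptic mouthwash, and this may confound the before-after comparison in specific objective 4 of the first main objective. It rests on two things in the Protocol: its own listing of mouthwash among agents that may alter the response, and the lack of an untreated periodontitis group. It also rests on one assumption, that at least one regular user enrols and stops at entry.

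The certain part is the exposure difference: 0 to 7 days off the rinse at baseline against about 49 days at follow-up. The resulting bias cannot be sized from the documents and may be small. This is a modest design gap worth closing because closing it is cheap. It is not a numerical error, and it does not show that the treatment comparison is invalid.

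**What to change.** Reconcile the two lists under 2.- Sample study by adding recent antiseptic mouthwash use to the entry exclusions, with a look-back window that the sponsor chooses and justifies. Check it on Day 0 from the hygiene-habits and medication history already listed under Clinical Parameters. In the same edit, reconcile the crevicular fluid sampling section with the Day 7 entry in the visit schedule, since the time off the rinse at baseline depends on which applies.

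The cost is a short change to the entry criteria, with no added visit, sample or staff. The downside is recruitment: some users would be screened out or enrolled later, and because the cases come from first visits, later enrolment can also mean that their study treatment starts later. The sponsor should weigh this when setting the window.

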## MATERIAL :

- Periodontal probe (Williams 10mm, Hu-Friedry ®)
- O-Ring radiographic parallelization system (Densply®)
- Intraoral radiography apparatus (E-wood®, Haigol-Dong, Korea)
- Perio paper strips ®: special paper strips to collect volumes of 0-1.2 ml crevicular fluid (Oraflow®, New York, USA)
- Periotron 8000®: electronic moisture micro-meter specially designed to assess the crevicular fluid, periodontal pocket fluid and salivary fluid (Oraflow®, New York, USA)
- Periotron professional: Software designed to pass the values given by Periotron 8000® to milliliters (Oraflow®, New York, USA)
- Δ 1.5 ml reaction vials (Ependorff®)
- Precision calibrated pipettes of 10-1000 µl and disposable tips (Ependorff®)
- Distilled or deionized water
- PBS (Phosphate buffer saline)
- Protease inhibitors (CN P8340 Sigma, Missouri, USA)
- Kit Elisa sRANKL and OPG (Biomedica Medizinprodukte®, Austria)
- Automatic plate washer
- ELISA reader with capacity to read absorbances from 450 nm to 620 nm.

## CLINICAL PARAMETERS:

- **Clinical history data:**

Patient's age Systemic pathologies Medication

Smoking habit

Hygienic habits (material, frequency, technique and time)

## Periodontal exploration:

Depth of probing: with a Williams millimetric manual periodontal probe, six points were recorded per tooth (disto-vestibular, mid-vestibular, mesio-vestibular, disto- palatal, mid-palatal, and mesio-palatal).

Recession: the distance from the amelocementary line to the gingival margin will be measured and recorded in the same points mentioned above (disto-vestibular, mid-vestibular, mesio-vestibular, disto-palatal, mid-palatal and mesio-palatal).

Clinical insertion level: Adding the aforementioned parameters we can find this parameter for each point.

Dichotomous index of bleeding on probing (Hemorrhage Index). Miller's mobility index.

Plaque index of Silness and Löe.

## Radiographic exploration:

In group cases, a complete radiographic series is made up of 18 radiographs of which 14 are periapical of incisors, canines, premolars and molars of all quadrants and 4 vertical bite fins of premolars and molars. All of them are performed with parallelized radiographic technique using the O-Ring parallelization system and intraoral X-ray apparatus.

In the control group, only two horizontal bite fins will be made to confirm the clinical diagnosis of absence of periodontal disease

